***Outcomes measured*:**

The primary endpoint will be combined all-cause mortality (ACM) or unplanned cardiovascular (CV) hospitalisation whichever came first.

The Endpoint Review Committee will adjudicate on :

1. the appropriate classification of cause of death, using data from primary and secondary care records, coroner reports and the death certificates. Mortality data will be obtained from the NHS Medical Research Information Service (MRIS)
2. underlying cause of hospitalisation using a standardised proforma and reviewing circumstances of hospitalisation from primary care records and hospital notes.

Secondary outcomes will include ACM, unplanned CV hospitalisation, CV mortality, unplanned CV hospitalisation, and unplanned hospitalisation.

*Quality of Life Assessment:* All participants will complete the SF-12, EuroQol (EQ5D), and Kansas Heart Failure Questionnaire (KHFQ) at enrolment, 3 months, 6 months, 12 months and 24 months. These will be administered by the study remote monitors. The initial quality of life forms will be completed at the time of patient enrolment in the hospital. Subsequent assessments will be performed by the patients in their homes. The forms will be sent to them by post with the necessary means for return of the forms. Receipt of the forms and their return will be managed by the remote monitors and local study administration staff. *Cost-effectiveness:* including cost of interventions, cost of Cardiovascular related health care.

Process measures will be collected to compare the pattern of care between the two arms and across centres (as we have no standardisation of usual care and the protocol is a pragmatic guideline and interpretation may differ between centres).

Key abnormalities detected in RM relate to atrial/ventricular arrhythmias and HF events. Key interventions are medication patterns, including anti-coagulation for atrial fibrillation.

There will be assessment of implementation of recommended interventions in the RM group and particularly those performed in primary care.

This flow chart summarises the study:

*- Acute care*

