***Interim analysis:***

We propose that the Independent Monitoring Committee (IMC) will review recruitment, data completeness and end points, and ensure no adverse effects from remote monitoring, at appropriate time points during the study.

For benefit we will use the primary outcome and Peto–Haybittle rule which uses a p value of p<0.001This is recommended by Pocock (Pocock SJ, Current controversies in data monitoring for clinical trials Clin Trials 2006;3:513e21) as it is conservative, would likely lead to a recommendation to stop only when there is a very convincing effect, thus preventing premature stopping of the trial, and it does not affect final analysis p values (final would be p=0.048) .

We plan one interim analysis based on primary events accumulated (at approximately 400 events).

For harm key outcomes will be ACM and any unplanned hospitalisation (e.g. if RM leads to over zealous use of diuretics leading to falls, acute renal failure) and we plan to undertake this interim analysis at the same time as benefit analysis.

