### 3.2.2 Secondary Endpoints

The secondary endpoints of the trial are:

1. Time to death.
2. Time to a cardiovascular related death.
3. Time to a non-cardiovascular related death.
4. Time to first unplanned hospitalisation for cardiovascular reasons or cardiovascular related death.
5. Time to first unplanned hospitalisation for non-cardiovascular reasons or death by any cause.
6. Time to first unplanned hospitalisation for cardiovascular reasons.
7. Time to first unplanned hospitalisation for non-cardiovascular reasons.
8. Total number of unplanned hospitalisations.
9. Total number of unplanned hospitalisations for cardiovascular reasons.
10. Change from baseline in SF12 scores at 2 years (physical and mental health components).
11. Change from baseline in EQ5D scores at 2 years.
12. Change from baseline in KCCQ at 2 years.
13. Change from baseline in SF12 scores at 1 year (physical and mental health components).
14. Change from baseline in EQ5D scores at 1 year.
15. Change from baseline in KCCQ at 1 year.
16. Number and cost of hospitalisations.
17. Difference in cost of resources consumed.
18. Difference in cost of cardiovascular related health care use.
19. Incremental costs per quality-adjusted life years (QALYs).

Unless otherwise stated, secondary endpoints will be measured at the last follow-up or at the last available observation within the two year follow-up period.

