## 4.4 Costs

The relevant costs are those of the intervention and of linked changes in the resources used related to HF. These include medications, devices, SAEs, any other HF related hospitalisations and use of community health services.

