### 4.4.2 Resource use data

Data relevant to the use of NHS resources were collected in five routine questionnaires headed:

1. Healthcare Utilisation Form,
2. System Modification,
3. SAE Hospitalisation,
4. Medication, and
5. Follow up interview.

These were administered at baseline, 3, 6 and 12 months and then yearly with the final collection at trial exit.

Levels of resource use by patient will be estimated under the following seven headings:

1. System modification (including reasons from a pre specified list)
2. CVD medication by 11 classes at start of study and new medication during the study with date. Other medication was recorded as yes/no.
3. Cardiac tests/procedures as day case admission
4. SAEs resulting in a hospitalisation, divided between those related to the study and not, along with duration of hospital stay
5. Hospital admissions (any other HF related hospitalisations other than SAEs)
6. Use of GP and practice nurses and Cardiac / HF Specialist nurses
7. Outpatient appointments and any A&E attendances.

Of these, 1) to 4) are plausibly related to the intervention while 5) to 7) refer to wider changes in health service use. For each of these items, the cost will be estimated as number of contacts multiplied by unit cost. The unit costs for GPs, practice nurses and Cardiac / HF nurses will be taken from PSSRU^5^. Hospital services costs, including for SAEs will be taken from National Reference costs. Drug costs by class will be taken from the BNF and PPA. The unit cost of system modifications will be based on that of an outpatient or day case contact as recorded in the trial. The cost of any A&E attendances will also be included.

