### 4.4.5 Incremental Cost-Effectiveness Analysis

The incremental differences in costs and effects will be compared between the intervention and control group and the incremental cost-effectiveness ratio (ICER) will be calculated using the formula: ICER = [costs (Intervention) – costs (control)] / [effects (intervention) – effects (control)].

Incremental costs and effects will be jointly bootstrapped and shown as a scatter plot on the cost effectiveness plane.

An ICER will be estimated for different levels of willingness to pay for a QALY using a cost effectiveness acceptability curve. Results will be compared with NICE’s threshold of £20,000 to £30,000.

The base case will be based on QALYs via EQ5D and NHS costs related to HF. Sensitivity analyses will include QALYs based on SF12 and on a range of monitoring costs based on different caseloads.

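### The cost scope of the base-case ICER is contradictory: HF-related costs in SAP 4.4 and 4.4.5, all SAE admissions in SAP 4.4.2 to 4.4.4, cardiovascular care in the protocol

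*Combined protocol and SAP*

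**What the plan says.** The sentence that defines the base case is in SAP 4.4.5: "The base case will be based on QALYs via EQ5D and NHS costs related to HF". The next sentence gives the accompanying analyses: "Sensitivity analyses will include QALYs based on SF12 and on a range of monitoring costs based on different caseloads". Neither varies which costs count.

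SAP 4.4 sets the same limit in general terms: "The relevant costs are those of the intervention and of linked changes in the resources used related to HF". It then lists the items: "These include medications, devices, SAEs, any other HF related hospitalisations and use of community health services".

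The operational sections are wider. Heading 4 of the resource-use list in SAP 4.4.2 is "SAEs resulting in a hospitalisation, divided between those related to the study and not, along with duration of hospital stay". The restriction to heart failure appears only under heading 5, which covers admissions that are not SAEs. SAP 4.4.3 prices SAE hospital days in each arm, and SAP 4.4.4 adds up intervention, hospitalisation and medication costs. Neither mentions heart failure as a condition for counting an admission.

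A third scope appears elsewhere. Protocol section 9 names "cost of Cardiovascular related health care" as part of the cost-effectiveness outcome. SAP 3.2.2 lists "Difference in cost of cardiovascular related health care use" as endpoint 18, after endpoint 17 on the cost of resources consumed. Endpoint 19, incremental cost per QALY, does not say which scope it uses.

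**The concern.** An ICER is coherent when its numerator and denominator cover the same events. Here the denominator comes from EQ5D, a generic instrument, by area under the curve (SAP 4.3 and 4.4.4), so any illness that changes a reported health state can change the QALYs. If the numerator holds only HF-related costs, an admission for another cause can lower the QALYs without adding to the costs.

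The trial itself regards such admissions as possible consequences of the intervention. The interim analysis text in protocol section 10 makes any unplanned hospitalisation a key harm outcome and gives the example "if RM leads to over zealous use of diuretics leading to falls, acute renal failure". The pathway also acts on atrial and ventricular arrhythmia and on anticoagulation, so stroke and arrhythmia admissions may change as well.

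At stake is the main economic result and its comparison with the NICE threshold. Two analysts following the same SAP could treat a fall or stroke admission differently and report different ICERs, each with text to support the choice.

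**Working it through.** **Step 1. What counts as an SAE.** Protocol section 17 includes any untoward medical occurrence that leads to death, an unplanned inpatient stay or a prolonged stay. Cause plays no part. An unplanned admission for a fall, a stroke or renal failure is therefore an SAE.

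**Step 2. How the Endpoint Review Committee (ERC) charter (SAP 7.1) classes the admissions in question, and which scope would price them.** The SAP does not say that costing will use the ERC class. The table assumes it would.

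| Admission | ERC class | HF only (SAP 4.4.5, literal) | CV (protocol section 9) | All SAEs (SAP 4.4.2 to 4.4.4) |
|---|---|---|---|---|
| Fall with no cardiovascular cause | Other (inferred; not named in the charter) | out | out | in |
| Renal or metabolic disturbance, no overt HF and no HF drug withdrawn | Other | out | out | in |
| Stroke (cerebral vascular disease) | CV, not HF | out | in | in |
| ICD shock | CV, not HF | out | in | in |
| Renal disturbance or symptomatic hypotension linked to HF medication | HF | in | in | in |

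The three scopes give different answers in four of the five rows. Only the last row is settled.

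**Step 3. Can the text be reconciled as it stands?** SAP 4.4 can be read two ways. SAEs are listed as an item in their own right, which suggests that all of them count. But the list is introduced as resources related to HF, and SAEs are followed by a reference to other HF-related hospitalisations, which suggests that only HF-related SAEs are meant. SAP 4.4.5 then repeats the HF limit. The wording does not decide the matter.

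**Step 4. Size, as illustration only.** The plan states no figure to reproduce. The inputs come from protocol Appendix I:

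- mean inpatient cost £771 per patient-year (95% CI £508 to £1,035);
- mean admissions 0.32 per patient-year;
- assumed QALY gain of 0.02 or 0.05 over one year.

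Cost per admission = 771 / 0.32 = £2,409. With the interval limits it is 508 / 0.32 = £1,588 and 1,035 / 0.32 = £3,234.

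Change in ICER = (net unpriced admissions per patient-year × cost per admission) / QALY gain. The net number of admissions is an assumption, because the documents give no value.

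| Net unpriced admissions per 100 patient-years | Cost per patient-year | Change at 0.02 QALY | Change at 0.05 QALY |
|---|---|---|---|
| 1 | £24 | £1,205 | £482 |
| 5 | £120 | £6,023 | £2,409 |
| 10 | £241 | £12,047 | £4,819 |

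For 5 per 100 at a 0.02 gain, the cost interval gives 0.05 × 1,588 / 0.02 = £3,970 to 0.05 × 3,234 / 0.02 = £8,085, or about £4,000 to £8,100. The threshold band runs from £20,000 to £30,000, a width of £10,000, so the central £6,023 is about 60% of that width.

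The change adds to the ICER if remote monitoring has more of these admissions than usual care, and subtracts from it if it has fewer.

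**The case against.** The strongest reply is that the sections that actually build the costs already include these admissions. SAP 4.4.2 collects SAE hospitalisations whether or not related to the study, SAP 4.4.3 prices their days, and SAP 4.4.4 adds hospitalisations without qualification. On that reading, HF-related in SAP 4.4.5 is loose shorthand. This is a fair reading, and it defeats a stronger inference that a reader might draw from SAP 4.4.5 alone: that admissions for the intervention's named harms definitely fall outside the ICER. The documents conflict on this; they do not establish the exclusion. The ERC charter also keeps renal disturbance and hypotension caused by HF drugs inside the HF class, so part of the named harm is priced even on the narrow reading.

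Two further inferences are tempting and unsupported.

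- The first is that HF-only costing favours remote monitoring because it keeps the savings and drops the offsets. It would equally drop savings from any stroke or arrhythmia admissions that the pathway prevents.
- The second is that unblinded site staff would decide which admissions are HF-related. Under protocol section 9 and SAP 2.4.3, the ERC adjudicates the cause of hospitalisation, and no passage describes staff sorting admissions by HF for costing.

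It can also be said that endpoints 16 and 17 carry no HF limit, so a non-HF cost difference could be seen there. That is true, but it would not be visible in the ICER, which is the figure compared with the threshold.

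What the reply leaves standing is the contradiction itself. SAP 4.4.5 is the sentence that governs the base case, and it says something different from the sections that feed it.

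**Conclusion.** The concern stands as a contradiction in scope, and it should be resolved before the economic analysis is run. Followed literally, SAP 4.4.5 omits non-HF unplanned admissions that EQ5D reflects and that the protocol treats as a harm outcome. Followed through SAP 4.4.2 to 4.4.4, it includes them. No named sensitivity analysis would show the difference.

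The direction of any error is unknown. Its size depends on an assumed net admission difference, on unit costs from 2003/4 in a population where ICDs were probably uncommon (Appendix I itself calls their representativeness unclear), and on a QALY gain that Appendix I only supposes. The illustration shows that the choice of scope could matter against the threshold. It is not evidence that the ICER is distorted.

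**What to change.** - In SAP 4.4 and 4.4.5, state that base-case costs include the intervention cost and all unplanned (SAE) hospitalisations of any cause, in line with SAP 4.4.2 to 4.4.4.
- Add two sensitivity analyses on cost scope, one with HF-related costs only and one with CV-related costs only. Say that the ERC classification defines both for admissions.
- State which scope endpoint 19 uses, and align endpoints 16 to 18 and the protocol section 9 wording with it.

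Widening the base case to every NHS cost on the five forms is more debatable and is not needed to remove the contradiction.

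The cost is a change of SAP wording and two extra runs. SAE hospitalisations and their length of stay are already recorded, so no new data are required. Any-cause admissions add variance unrelated to the intervention, so the interval around incremental cost will be somewhat wider.

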# Section 5. Adverse events

## 5.1 Adverse event collection

It is believed that there is no increased risk to REM-HF trial patients, as they will have access to currently available care pathways when required but will have the additional advantage of immediate but remote expert monitoring. However, the study will evaluate the acceptability of such monitoring to patients through any adverse impact on quality of life. Adverse events for this study are not being actively collected. The trial participants (or guardians of the trial participants) are however encouraged to report any serious adverse event by contacting the study team by telephone. They are also recommended to contact the GP or emergency service.

## 5.2 Serious adverse event monitoring

In agreement with the Sponsor of this study, all AEs that are classified within GCP as "serious" and that result in hospitalisation or death will be considered an SAE, documented in the ECRF and reviewed by an appropriately trained member of the research team. Where an SAE is assessed as being related to study procedures, the reporting will be escalated to the Sponsor and the concerned hosting R&D Department. SAEs not related to the study intervention will be documented in the eCRF but will not be escalated to the Sponsor or hosting R&D.

An Independent DSMB will review recruitment, data completeness, and endpoints, and to monitor any occurrence of serious adverse effects from remote monitoring, at appropriate time points during the study. Trial procedures also specify that the remote monitoring staff will review any available data in the light of an adverse event. The trial manager will also collate all protocol deviations and serious adverse event data reported by the remote monitors.

## 5.3 SAE reporting

All SAEs will be coded according to the latest version of MedDRA available. The data management team may wish to group MedDRA codes further into more clinically meaningful groups to aid interpretation.

All reported adverse events will be tabulated by treatment pathway. These will be separated into two tables: treatment related serious adverse events and serious adverse events that weren’t considered to be related to treatment. The number of participants who discontinue or who are withdrawn due to an SAE will also be tabulated.

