# 17. Safety Issues

Many of the study participants will have chronic illnesses and will be receiving treatment for heart failure and arrhythmias. Due to their illness, prolonged hospitalisation and re-admissions to hospital will be commonly occurring events during clinical care.

Similarly, study participants with (severe) underlying heart disease are at risk of dying during the course of the study as a result of the natural history of their disease/age.

In agreement with the Sponsor (Southampton) of this study, all Adverse Events including those normally classified within GCP as "serious" and result in hospitalisation or death will be documented in the ECRF and reviewed by an appropriately trained member of the research team. An SAE according to this protocol is considered to be any untoward medical occurance that results in death, requires inpatient unplanned hospitalisation or prolongation of existing hospitalisation. These Serious Adverse Events (SAE’s) will be assessed by a medically qualified team member.  Where an SAE is assessed as being related to study procedures, the reporting will be escalated to the Sponsor and the concerned hosting R&D Department. SAE’s not related to the study intervention are documented in the ECRF but will not be escalated to Sponsor or hosting R&D.

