### 6.1.2 Planned Outcome tables

Table 5: Hazard ratios for Primary and Secondary Time to Event Endpoints (ITT population).

Table 6: Relative risks for number of hospitalisations (ITT population).

Table 7a: Change in QoL scores from baseline to 2 years (ITT population).

Table 7b: Change in QoL scores from baseline to 1 year (ITT population).

Table 8: Health Economics Outcomes.

Tables 9 to 63: Replicates of Tables 5, 6, 7a, 7b and 8 in each of the 11 pre-specified subgroups (ITT population).

Tables 64 to 68: Replicates of Tables 5, 6, 7a, 7b and 8 (PP population). – Including Multiple Imputation results where applicable.

Table 69: Treatment related serious adverse events (ITT Population).

Table 70: Serious adverse reactions not considered related to treatment (ITT Population).

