**Unplanned Cardiovascular Hospitalisation for heart failure**

Unplanned hospitalisation due to heart failure or primarily for its treatment, or if heart failure was a major component of the patient’s hospital admission. A patient admitted for this reason must have symptoms and/or signs of worsening heart failure, ongoing or worsening in the prior 3 months, and been treated with additional oral or intravenous diuretics.

Evidence of worsening heart failure has to include at least one of the following items: increasing dyspnoea on exertion, orthopnoea, nocturnal dyspnoea or paroxysmal nocturnal dyspnoea, increasing fatigue or decreasing exercise tolerance, raised jugular venous pressure and/or increasing peripheral oedema, and/or radiological signs of pulmonary oedema or as judged by the ERC.

The following are examples fulfilling these admission criteria:

- clinical signs of heart failure recorded on admission with a chest infection
- symptomatic hypotension associated with HF medication
- significant metabolic / renal disturbance associated with heart failure or the medication for heart failure, with or without symptoms
- transplant assessment
- device upgrade to CRTD in the presence of heart failure symptoms or signs

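### SAEs are shown by arm only after a split on a relatedness judgement with no stated blinding, and no all-SAE table by term and arm is listed

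*Combined protocol and SAP*

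**What the plan says.** SAP 5.3 codes all SAEs in MedDRA, lets the data management team group codes further if it wishes, and tabulates events by pathway. It then divides the display: "These will be separated into two tables: treatment related serious adverse events and serious adverse events that" were judged unrelated. SAP 6.1.2 lists the two results as "Table 69: Treatment related serious adverse events (ITT Population)" and "Table 70: Serious adverse reactions not considered related to treatment (ITT Population)". They are the only SAE tables listed. The outcome shells in SAP 7.4 stop at Table 7b, so the layout of Tables 69 and 70 is not given, nor is it stated whether they count patients or events.

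On who judges relatedness, Protocol section 17 says that SAEs "will be assessed by a medically qualified team member". SAP 5.2 has them reviewed by a trained member of the research team, and adds: "Where an SAE is assessed as being related to study procedures, the reporting will be escalated to the Sponsor". SAP 1.2.2 describes the trial as open label. Neither document states that the relatedness assessor is blinded. The Endpoint Review Committee classifies causes of death and hospitalisation; neither document gives it the relatedness decision.

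On harm, the interim analysis text in Protocol section 10 names all-cause mortality and any unplanned hospitalisation as the key outcomes, with an example: "if RM leads to over zealous use of diuretics leading to falls, acute renal failure".

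**The concern.** A comparison of a harm between arms is protected by randomisation only if events enter the table by a rule that does not depend on arm. Relatedness is judged after randomisation, apparently with the arm known. The criterion is variously relation to study procedures, to the study intervention or to treatment, and no rule says how a UCP event could qualify. So the label may attach mainly to RCP events. In that case Table 69 makes RCP look worse for a given type of harm and Table 70 makes it look better, and neither alone compares the arms as randomised.

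At stake is how a reader judges specific harms of more intensive management. The protocol's own example is over-diuresis. The remote-monitoring handbook (Protocol Appendix II, section 4) also prompts anticoagulation, so bleeding is of interest too. The direct check is each type of event by arm regardless of relatedness, and the table list does not include it.

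**Working it through.** The plan states no figure on this point, so there is none to reproduce. The check is how far the split can move a by-type comparison.

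**Inputs.** 825 patients per arm (SAP 1.2.2). Everything else is an assumption: f, the share of RCP events of one type called related; g, the same share in UCP; and the frequency of the harm.

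**General form.** With true event ratio R (RCP/UCP):
- Table 70 ratio = R × (1-f)/(1-g)
- Table 69 ratio = R × f/g
- Tables 69 and 70 added = R, whatever f and g are

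If f = g there is no distortion. With g = 0, Table 70 shows R × (1-f) and Table 69 shows RCP events against none.

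**No true difference (R = 1, g = 0).** Table 70 shows 1.00 at f = 0, 0.98 at 2%, 0.90 at 10% and 0.75 at 25%.

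**A true doubling (R = 2, g = 0).** The 95% limits are ratio × exp(±1.96 × √(1/a + 1/b)), for Poisson counts a and b.

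Harm in 5% of UCP: 0.05 × 825 = 41.25 events, against 82.5 in RCP.

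| f | Table 69 (RCP v UCP) | Table 70 (RCP v UCP) | Table 70 ratio (95% CI) |
|---|---|---|---|
| 10% | 8.25 v 0 | 74.25 v 41.25 | 1.80 (1.23 to 2.63) |
| 25% | 20.6 v 0 | 61.9 v 41.25 | 1.50 (1.01 to 2.22) |

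Added, both rows give 82.5 v 41.25, ratio 2.00 (1.38 to 2.91).

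Harm in 2% of UCP: 0.02 × 825 = 16.5 events, against 33 in RCP.

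| f | Table 70 (RCP v UCP) | Table 70 ratio (95% CI) |
|---|---|---|
| 10% | 29.7 v 16.5 | 1.80 (0.99 to 3.29) |
| 25% | 24.75 v 16.5 | 1.50 (0.80 to 2.80) |

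Added, 33 v 16.5, ratio 2.00 (1.11 to 3.61).

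**Smaller excess.** With 10% in UCP (82.5 events), 12.5% in RCP (103.1) and f = 20%, Table 70 shows 103.1 × 0.8 = 82.5 v 82.5. The 25% excess is gone from that table, while Table 69 shows 20.6 v 0.

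**What adding the tables recovers.** Event counts add exactly. Patient counts need not. If Table 69 has a patients with a given event and Table 70 has b, the number with at least one lies between the larger of a and b and a + b. Were the figures of 20.6 and 61.9 above patient counts, that range would be 61.9 to 82.5.

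**The case against.** The strongest reply is that the plan's test for harm lies elsewhere. The protocol's harm outcomes are all-cause mortality and any unplanned hospitalisation; falls and renal failure are only examples of why the second was chosen. Both have unsplit counterparts among the SAP 3.2.2 endpoints (items 1 and 8), compared as randomised. An SAE here is a death, an unplanned admission or a prolonged stay, so item 8 holds every admission for over-diuresis. This stands, and it settles overall safety.

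It does not supply a by-type display. Item 7, "Time to first unplanned hospitalisation for non-cardiovascular reasons", is also unsplit, but the ERC charter files one form of the same harm ("significant metabolic / renal disturbance associated with heart failure or the medication for heart failure, with or without symptoms") under heart-failure hospitalisation and other renal disturbance under non-cardiovascular admission. The component endpoints are therefore not a comparison by type of harm.

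Second, nobody knows f. Protocol section 3 and SAP 5.1 expect no increased risk, so few events may be called related and the distortion may be trivial. This also stands. The 10% and 25% cases are illustrations.

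Third, a reader might infer that the split would hide a harm. The documents do not support that. All reported events are tabulated, both tables are ITT, and the counts can be added. In the doubling at 5%, Table 70 alone still excludes 1 and Table 69 points the same way. Only at the rarer 2% does Table 70 alone fail to exclude 1.

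Fourth, SAP section 6 promises additional tables, SAP 5.3 permits grouping, and the data monitoring board may define its own reports. These leave room for a combined table but commit to none. Groupings chosen after results by arm are visible carry less weight than ones fixed beforehand.

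**Conclusion.** The point holds as a limited weakness in presentation. The SAE tables listed depend on a judgement for which no blinding is stated, in an open-label trial, and neither is by itself a comparison of the arms as randomised. If the related label falls mainly on RCP events, Table 70 is tilted towards RCP by 1-f and Table 69 against it. That premise is an inference, f is undocumented, and at f near 0 the effect disappears. The more certain loss is that the number of patients with a given type of SAE may not be recoverable from the two tables.

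No endpoint or estimate is affected. It would be wrong to conclude that the trial lacks a valid safety comparison, or that falls and renal failure were prespecified harm endpoints left unanalysed: the documents give them only as examples. This is a cheap improvement worth considering.

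**What to change.** In SAP 5.3 and 6.1.2, make the main SAE table all SAEs by randomised arm regardless of relatedness, by MedDRA system organ class and preferred term. Give both patients with at least one event and event counts. Before database lock, write down any grouped terms to be used under SAP 5.3, for example renal/electrolyte, hypotension/syncope/falls, and bleeding. Keep Tables 69 and 70 as supplementary displays.

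The cost is one extra table and a short list of grouped terms. SAE data are already collected (SAP 4.4.2) and MedDRA coding is already planned, so no new data are needed.
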